### Study monitoring and interim analysis

A Trial Steering Committee meets every 6 months and will be responsible for drafting the final report and submission for publication. The monitoring reports are submitted to and reviewed by the data and safety monitoring committee every 6 months. Soon after recruitment had started, a data and safety monitoring committee met at the start of the trial to establish a charter, and will continue to meet at least annually to determine if there are any ethical problems.

To evaluate the safety of this trial, one interim analysis was planned. The interim analysis tested the hypothesis that the TLDG- and LADG-associated morbidity in this trial did not differ significantly from the morbidity reported in previous studies on open gastric cancer surgeries.

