## Methods

### Objectives

The primary endpoint of this study is to assess whether TLDG is superior than LADG in terms of the short-term morbidity. The secondary research endpoint is to compare TLDG and LADG in terms of the quality of life (QOL).

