### Sample size calculation

This trial is designed to compare TLDG and LADG in terms of the short-term morbidity and QOL. According to interim results of the multi-institutional prospective study (KLASS 01) that is reported in 2010, the complication rate after the LADG was 11.6% [3], while it was 16.4% according to another prospective single-institutional study reported in 2015 [15]. In addition, according to the final outcomes of KLASS 01 study, the incidence of postoperative complication was 13% [16]. Estimated shor-term complication rate for LADG based on the previous results mentioned above is 13.6%. On the other hand, according to the recent studies on short-term clinical outcomes of TLDG [10, 15, 17], the short-term complication rate of TLDG was expected to be 7.5%. Therefore, the two surgical methods might show the morbidity differed by 6.1%. The hypothesis to be tested is that the 30-day morbidity rate of TLDG is 6.1% less than that of LADG. Allowing for a dropout rate of 10%, the planned sample size was 442, with 221 cases per each arm. This will provide a power of 80% to reject the null hypothesis with a significance level at less than 0.05.

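### The one interim safety analysis tests each operation against published open-surgery morbidity for non-significance and does not compare the two randomised arms

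*Protocol article*

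**What the plan says.** The section on study monitoring and interim analysis states: "To evaluate the safety of this trial, one interim analysis was planned". The hypothesis for that look is that morbidity with TLDG and with LADG "did not differ significantly from the morbidity reported in previous studies on open gastric cancer surgeries". The section thus fixes the comparator (published open-surgery results) and the criterion (no significant difference). It gives no open-surgery rate, interim size, significance level or sidedness, and it attaches no decision to either result.

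The trial's own question is different. Under Objectives, the aim is to "assess whether TLDG is superior than LADG in terms of the short-term morbidity", and patients are randomised 1:1 between these two operations. There is no open-surgery arm. The sample size section assumes 30-day morbidity of 13.6% for LADG and 7.5% for TLDG, with 221 patients per arm.

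Other oversight exists: "The monitoring reports are submitted to and reviewed by the data and safety monitoring committee every 6 months". The committee also has a charter, which is not shown, and it meets at least annually.

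**The concern.** For patients being enrolled, the safety question that randomisation can answer is whether one operation causes more morbidity than the other. A concurrent randomised comparator is available, yet the stated hypothesis sets both arms against results from other patients, surgeons and studies.

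Three features cause difficulty:

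- **Comparator.** Two separate comparisons with an external rate do not estimate the difference between the arms. Pooling the arms against that rate would not either.
- **Criterion.** A non-significant result does not show that morbidity is acceptable. The smaller the interim sample, the wider the range of rates that counts as not different.
- **Direction.** The wording is two-sided in effect, so an arm can depart from the open-surgery rate by doing better. For a safety look that signal is ambiguous.

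At stake is how far the one formal safety look can be relied on. The final TLDG-versus-LADG analysis is not affected.

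**Working it through.** The interim analysis states no figure of its own to reproduce. The check asks what its rule allows.

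**Inputs.** From the sample size section: LADG 13.6%, TLDG 7.5%, 221 per arm. Assumed, because the article does not give them: interim size (100 per arm, or 110, about half of 221), open-surgery rate (10% to 20%), and a two-sided 0.05 level.

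**Step 1: which results meet the criterion.** For an arm with x events in n patients and open rate p0, test H0: p = p0 with the exact two-sided binomial test. The arm meets the criterion if the p-value exceeds 0.05. With n = 110 and p0 = 0.136, the p-values are:

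- x = 7: 0.025; x = 8: 0.051
- x = 22: 0.069; x = 23: 0.035

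So 8 to 22 events (7.3% to 20.0%) meet the criterion.

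**Step 2: compare the arms at the ends of that range.** The last column is Fisher's exact test between an arm at the lower end and an arm at the upper end, n = 110 per arm.

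| Assumed open rate | Events that meet the criterion | Fisher p between the extremes |
|---|---|---|
| 10% | 5 to 17 | 0.012 |
| 12% | 7 to 20 | 0.013 |
| 13.6% | 8 to 22 | 0.0097 |
| 15% | 10 to 24 | 0.014 |
| 18% | 12 to 27 | 0.013 |
| 20% | 14 to 30 | 0.011 |

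In the 13.6% row the difference is 22/110 − 8/110 = 14/110 = 12.7 percentage points. Its standard error is √(0.200 × 0.800/110 + 0.073 × 0.927/110) = 0.0455, so the 95% interval is 12.7 ± 1.96 × 4.55, or 3.8 to 21.6 points. The stated hypothesis would not bring this out. At 100 per arm the extremes give p = 0.012 to 0.019 over open rates of 10% to 20%.

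**Step 3: sensitivity to harm, starting from the protocol's LADG rate.** Take LADG at 13.6% and TLDG doubled to 27.2%, with 100 per arm. The chance that the planned test flags TLDG as too high is P(X > upper limit), with X ~ Bin(100, 0.272).

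| Assumed open rate | Flagged from | Probability |
|---|---|---|
| 13% | 21 events | 94% |
| 15% | 23 events | 86% |
| 18% | 26 events | 64% |
| 20% | 29 events | 38% |

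For the direct comparison, power = Φ[(d − z·s0)/s1], with

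- d = 0.272 − 0.136 = 0.136
- mean rate 0.204, s0 = √(2 × 0.204 × 0.796/100) = 0.0570
- s1 = √[(0.136 × 0.864 + 0.272 × 0.728)/100] = 0.0562

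Two-sided (z = 1.96): Φ(0.43) = 67%. One-sided (z = 1.645): Φ(0.75) = 77%.

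At open rates of 13% to 15% the planned test is the more sensitive. At 18% to 20% it is the less sensitive.

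**Step 4: rejection because an arm does well.** At 100 per arm and an open rate of 15%, the lower limit is 9 events. With TLDG at its planned 7.5%, P(X ≤ 8) = 0.665. TLDG would then differ significantly from open surgery about two times in three simply by performing as the protocol expects (69% at 110 per arm).

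**The case against.** The strongest reply has four parts.

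1. **The external benchmark has a purpose.** A between-arm comparison cannot show that morbidity is too high in both arms, and a comparison with open surgery can. The Background also reports no significant morbidity difference between open and laparoscopic gastrectomy in the group's earlier trial. This stands, and it is why the open-surgery comparison should be kept.

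2. **The planned test is not weak in general.** A reader might infer that it would usually miss harm from TLDG. The documents do not support that. The answer turns on an open rate and an interim size that the article does not state, and at open rates of 13% to 15% the planned test detects a doubling from 13.6% more often than the direct comparison does. This stands.

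3. **The interim analysis is not the whole of safety oversight.** A reader might also infer that nobody will compare the arms for harm, or that TLDG will be declared safe on a non-significant result. Neither follows. The committee sees reports every 6 months under a charter that is not shown, and the article attaches no decision to the interim result. Harm guidance and stopping boundaries commonly sit in a charter or full protocol, so their absence here is not a fault.

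4. **A bare non-significant comparison between arms would prove nothing either.** This is correct. At 110 per arm its two-sided power for 20% against 13.6% is only 24%. What is needed is an estimate with an interval.

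None of this answers the remaining point. The article does state a comparator and a criterion for its one formal safety look. That comparator leaves out the randomised contrast, and that criterion is non-significance in either direction.

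**Conclusion.** The concern holds as a fault of comparator and criterion. As worded, the interim hypothesis can be met by both arms while they differ significantly from each other (p about 0.01 to 0.02 at the extremes, for 100 or 110 per arm and open rates of 10% to 20%). It can also be rejected because TLDG does well: about 67% of the time at 100 per arm, if TLDG is at its planned 7.5% and the open rate is 15%.

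The qualitative conclusion rests on the text alone. The figures rest on the assumed open rate, interim size and two-sided 0.05 level. They illustrate what the rule permits and do not predict how it will perform. The point should be corrected, but it does not threaten the primary analysis.

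**What to change.** In the section on study monitoring and interim analysis:

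- **Add** the randomised TLDG-minus-LADG difference in 30-day morbidity with its confidence interval, seen only by the data and safety monitoring committee and judged against the harm guidance in its charter.
- **Restate** the open-surgery comparison as each arm's morbidity with a confidence interval, set beside a named reference rate and looking for excess morbidity. Keep it as an external check, and do not read a non-significant result as a pass.
- **State** that no efficacy test is made at this look, so the final 0.05 level is unchanged.

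The cost is a change of wording and a little more analysis. The 30-day morbidity data are already collected for the primary endpoint, and no efficacy alpha is spent. The drawback is that an unblinded between-arm result will exist during the trial, so it must be confined to the committee.

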### Progress

The actual enrollment will be ended at the time when the planned sample size is achieved.

## Discussion

As we described above, we named this study as KLASS 07. KLASS is a time-honoured study group that has established laparoscopic surgery for gastrointestinal disease in Korea, and has performed some important RCTs for the rationale of laparoscopic gastrointestinal surgery. In 2016, KLASS group admitted the launching of KLASS 07 study, since they agreed with the necessity of RCT to compare the QOL between LADG and TLDG.

However, even though it is general to define the primary endpoint as QOL score, the short-term morbidity was designated as the primary endpoint of KLASS 07. There are 2 representative reason for this: i) First, regarding this subject, there has been few comparative result about QOL, and therefore we could not find any reference for sample size calculation. ii) Second, in the most of previous studies, the score of QOL questionnaire is not so different between the patients. Thus, it is difficult to provide the difference regarding superiority of non-inferiority, by which investigators find the rationale of sample size. Here, from our clinical experience, we expect that short-term morbidities have a strong effect on QOL of patients who underwent surgery, regardless of the type of surgery. With these reasons in mind, we defined the primary endpoint as “30-day morbidity”.

Although Woo et al. [15] previously reported a result of RCT regarding this topic, KLASS 07 embeds some discriminating values due to the following reasons.

First, it is necessary to perform multi-center RCT to compare the QOL between TLDG and LADG. To contemplate the superiority of one side or equality between both sides, we should get the universality of the surgical performance. It is not rational to conclude with the result of single institute, because one surgeon’s experiences do not representate the clinical outcomes of laparoscopic gastrectomy performed by many gastrointestinal surgeons. In addition, according to the current recommendation regarding the clinical evidence the previously performed single center RCT can be classified as ‘small RCTs with unclear results’, and deserves to level II evidence [18]. To acquire a level I evidence, we should perform a multi-center RCT [18]. The steering committee of KLASS 07 has already recruited 31 surgeons of 26 institutes.

Another value of KLASS 07 is also correlated with the universality. Regarding this comparison between LADG and TLDG, it is not sufficient to conclude with the limited number of patients. Woo et al. [15] involved only 55 patients in each arm. This sample size was defined based on one retrospective study (Tanimura et al. [19]’ study). In order to acquire the reliable basis for sample size calculation, we referred to 5 literatures (3 prospective studies and 2 retrospective studies), including the interim and final results of KLASS 01 study.

Furthermore, other than the QOL outcomes, KLASS-07 study additionally deals with the endoscopic findings and cost issues. The endoscopic findings will be investigated based on RGB classification, in which the food residue, gastritis, and bile reflux were systematically investigated. This subjects are known to be deeply related with QOL of patients, and therefore it should be investigated by an multi-institute RCT. In addition, our protocol suggests the diverse types of reconstructions, including Billroth II (with or without Braun anastomosis), Roux-en-Y gastrojejunostomy, and uncut Roux-en-Y gastrojejunostomy. Therefore, we can compare these reconstruction methods in terms of the clinical outcomes and QOL, acquire the information regarding the trend of reconstruction. Although the several literatures showed the lower incidence of gastritis and bile reflux in Roux-en-Y reconstruction than Billroth II [20–23], there has been no multi-center RCT regarding this issue. In addition, most of these studies did not explain the role of Braun anastomosis in patients underwent Billroth II reconstruction during laparoscopic gastrectomy. Moreover, as KLASS-07 study deals with laparoscopic procedure, in which postoperative adhesion less caused, we planned to analyze the relationship between the reconstruction method and internal hernia.

In addition, regarding the reconstruction method, KLASS-07 study protocol reflects the current status of gastric cancer surgery. Unlike the 2000 s when KLASS-01 study was ongoing, surgeons’ preferences to the reconstruction methods have changed after introducing TLDG. This trend is the reason why we exclude Billroth I reconstruction from KLASS-07 study. According to the results of Korean Gastric Cancer Association Nationwide survey in 2014, Billroth I reconstruction was less adopted in TLDG (35.1%) than LADG (66.9%) [24]. In other words, since TLDG was introduced, gastrojejunostomy-based reconstructions (i.e. Billroth II, Roux-en-Y gastrojejunostomy, and uncut Roux-en-Y gastrojejunostomy) have increased and Billroth I have decreased. With these reasons, Billroth I reconstruction was regarded to be a confounder in RCT comparing TLDG and LADG, although we could not confirm the obvious reason of avoiding Billroth I during TLDG.

## Conclusions

This multi-center RCT is still required to determine whether there are significant and quantifiable differences between the QOL of TLDG and LADG. The KLASS 07 trial is the first multi-center RCT regarding this topic. The findings from this trial are expected to be the critical clues for designing the detailed procedures during laparoscopic surgery for gastric cancer.

## Abbreviations

ASA: American Society of Anesthesiologists physical status classification
BMI: Body mass index
ECOG: Eastern Cooperative Oncology Group
EGC: Early gastric cancer
EORTC: European Organisation for Research and Treatment of Cancer
KLASS: The Korean Laparoendoscopic Gastrointestinal Surgery Study group
LADG: Laparoscopy-assisted distal gastrectomy
QLQ-C30: Quality of Life Questionnaire – Core Questionnaire 30
QOL: Quality of life
RCT: Randomized controlled trial
RGB: Residue, Gastritis, and Bile
STO22: The Stomach 22 module
TLDG: Totally laparoscopic distal gastrectomy
